The breach of confidentiality is a possible risk. Confidentiality will be maintained by numerically coding data, by disguising identifying information, and by keeping all data in locked file drawers. All information obtained from subjects will be accessible only to research staff. All staff will be trained in confidentiality procedures, and routine refreshers provided.

Safety parameters: The treatment is safe, and no case of vitamin D toxicity has ever been documented for cholecalciferol below 10,000 IU/day or higher. Based on the Mayo Laboratory Guidelines for 25(OH)D, the upper limit of normal is 80 ng/mL (Mayo Clinics Reference Laboratory, Rochester, MN). Operationally, we will stop vitamin D_3_ supplementation when if circulating 25(OH)D has exceeded 80 ng/mL serum 25(OH)D; or [2] > 2.75 mmol/L serum calcium. In recently completed studies involving high dose vitamin D_3_ supplementation resulting in circulating levels of 25(OH)D exceeding 300 nmol (120 ng/mL), there has been no evidence of hypercalciuria, the first indicator of hypervitaminosis D(20) For the purposes of this trial, however, to ensure maximal safety, we have included an upper limit of circulating 25(OH)D of 80 ng/mL, above which, supplementation will be discontinued.

Definition of adverse event and serious adverse event: The major risk of the study is symptoms of hypercalcaemia and hypervitaminosis D. To assess safety among those who are eligible and enroll participants will be informed on potential symptoms of hypercalcemia and asked to call the study coordinator if he or she experiences any such symptoms. Further, we will assess symptoms at the beginning of each month when the next month’s supply of pills is provided, and at week 2 of each month when participants are called to assess problems and adherence. Any symptoms noted will be reported to the study physician, who will make a determination if any reported symptoms are possibly related to vitamin D toxicity. If toxicity due to hypervitaminosis D or hypercalcemia is deemed a possibility, the participant will be asked to discontinue taking the pills and a blood sample for 25(OH)D and calcium will be taken. The local study doctor will determine whether further treatment is necessary.

Adverse event (AE) reporting: If a child is sick, s/he will be evaluated by the local school doctor, who will examine the symptoms. The physician will report immediately to Drs. [name] and [name] his/her opinion of whether the illness/symptom reported is related to the trial. [name] will report to the ERB and to the HSPH HSC the details of the symptoms and the If a child is sick, s/he will be evaluated by the local school doctor, who will examine the symptoms. The physician will report immediately to Drs. [name] and [name] his/her opinion of whether the illness/symptom reported is related to the trial. [name] will report to the ERB and to the HSPH HSC the details of the symptoms and the local doctor’s opinion of the likelihood that the adverse event is related to participation in the trial (“likely association with participation”, “unlikely association with participation”, “unknown association with participation”). A case report of the adverse event will be generated and submitted to the HSPH HSC and to the Ministry of Health ERB in Mongolia. We will communicate these events as quickly as possible.

We will report adverse events according to OHRA’s Adverse Event Reporting policy: Adverse events that are serious, unexpected and related or possibly related will be reported to the IRB within 7 calendar days from the time the investigator becomes aware of the event.  Any unexpected and study-related death will be reported to OHRA within 24 hours of the investigator’s knowledge of the event by e-mail or telephone. All non-serious adverse events that are unexpected and related or possibly related to the research will be submitted to the IRB within 21 calendar days from the time the investigator becomes aware of the event.
AE/SAE follow-up: If a child is sick, s/he will be evaluated by the local school doctor, who will grade the symptoms according to the chart with Adverse Event Grades. The physician will report immediately to Drs. [name] and [name] his/her opinion of whether the illness/symptom reported is related to the study. [name] will report to the ERB and to the HSPH HSC the details of the symptoms and the local doctor’s opinion of the likelihood that the adverse event is related to participation in the study (“likely association with participation”, “unlikely association with participation”, “unknown association with participation”). Course of action at report of Grade 1 toxicities will be decided on a case-by-case basis. The pediatrician of the child, if s/he was not the person who did the initial evaluation, will be notified of any Grade 2 toxicities. A case report of the adverse event will be generated and submitted to the HSPH HSC and to the Ministry of Health ERB in Mongolia. We will communicate these events as quickly as possible. The only special circumstances are the time zone difference between Ulaanbaatar and Boston, which can slow communication.

Mongolia that approved through OHRP as an FWA, we also propose to convene a DSMB comprised of Mongolian and American scientists to monitor the data as it accumulates from the study. The DSMB will have the authority to stop any intervention arm if they determine that it is having an adverse impact on participant health. In particular, we will ask the DSMB to monitor vitamin D levels to determine whether is causing a clinically plausible and statistically significant adverse effect.

DSMB Schedule. We propose that the DSMB meetings by conference call to decide the “stopping rule” protocol. A detailed Data and Safety Monitoring Plan will be submitted to the ERB and the Harvard Human Subjects Committee for approval prior to the recruitment of participants. During the intervention, serum samples will be taken according to the schedule. Samples will be immediately forwarded to the Health Science University laboratory for analysis, to provide timely data to the DSMB. The study biostatistician and PI will prepare reports for the DSMB, including data on participant recruitment, retention, compliance, and adverse events. The DSMB will meet at least twice during the course of the study.

Source documentation: Our source documentation include original documents, data, and records (clinical and office charts, laboratory notes, subjects’ evaluation checklists, copies or transcriptions, records kept at the labs involved in the study. We will maintain records of our study for five years after the study in the locked files and password-protected computers of the Harvard School of Public Health and Health Science University of Mongolia

LIST OF APPENDICES:

Letter to parents describing the study

Script for the evening meeting with parents and children explaining the study

Baseline background questionnaire and follow-up

Child Study Evaluation Form

Parent Study Evaluation Form

Food Checklist

Vitamin D Results Feedback Letter

HSPH HSC Human subjects pamphlet: Mongolian version

Consent Form

Assent Form

Excerpt from K99/R00 grant application of pilot study to NIH

1. Statistical Analysis

Prior to formal analysis, preliminary analysis will include plotting the collected data to search for data and laboratory outliers.

We will then examine the following covariates to gauge the success of randomization:

- Child age in months
- Household socioeconomic status
- Baseline height, weight, and adiposity
- Baseline vitamin D

Our main analysis tool will be a relatively simple differences-in-differences approach: we will calculate the differences between the pre-intervention and post-intervention levels within each child and then compare means between the groups. This analysis will be accomplished using a simple t-test, as each pairwise comparison of treatment arms is of independent interest. In the event of meaningful violations of t-test assumptions, we will use the familiar nonparametric Wilcoxon test for differences between two groups.

1. Sample Size and Power Calculation:

We designed the feasibility pilot to generate preliminary data for a later application. As this study is a feasibility pilot, the population is chosen to represent the characteristics of the schoolchildren we would recruit for a larger, longer study. Number of subjects are limited by the budget on one hand and on the other hand, determined by vitamin D mean and SD change based on our preliminary data. We calculated to have 80% power to detect minimum detectible difference of 2.63 ng/ml and 90% power to detect minimum detectible difference of 3.89 ng/ml in mean vitamin D between the pre- and post-intervention arms with an alpha error of 0.05. In the table below, we show the minimum detectible difference in mean vitamin D between the post-intervention arms, setting Type 1 error (alpha) to 0.05 and Type 2 error (beta) to 0.80 and 0.90. We used PASS statistical software for our calculations. We considered standard deviations in 25(OHD) levels from our pilot study data, in which we observed mean + s.d. 25(OHD) levels of 17.3 + 4.8 at the outset of the intervention and 26.5 + 4.5 at the end of the one month intervention in Ulaanbaatar. However, as we lack estimates of the expected effect of antimicrobial and cathelicidin induction assay baseline levels and degree of change with the intervention, we have refrained from generating speculative power calculations for the assay.

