That improving vitamin D status among healthy children will enhance innate immune response and will protect against TB infection.

A. To recruit subjects, obtain consent, distribute vitamin D supplements to the children in the schools, obtain biologic specimens and to transport those specimens intact back to the United States.

B. To test the hypothesis that daily vitamin D supplementation will increase plasma levels of 25(OH)D, an excellent measure of compliance, and restore TLR-induced antimicrobial activity in monocytes/macrophages tested in vitro.

Overview: We propose a feasibility pilot study with the aim to develop a full prospective study to investigate whether supplementation of vitamin D-deficient individuals with an oral vitamin D can reduce TB infection rate. Specifically, the effect of a daily 800 IU vitamin D supplement will be examined in a randomized trial: Mongolian adolescent children will be randomized to receive a daily vitamin D supplementation and placebo from the start of the study and followed through one school year.

1. Procedure and Intervention

Study design (e.g., double-blind, placebo-controlled, parallel design):

Pilot study to develop the details of the double-blind, placebo-controlled randomized trial of vitamin D in the prevention of TB infection

**Study endpoints:** the primary endpoint for this study is feasibility: 1) recruitment and consent of subjects 2) acquisition of data: height, weight, BMI, survey information (baseline background questionnaire and questionnaire regarding respiratory infection and eczema) and blood 3) compliance with the protocol 4) feasibility of shipping serum samples to the United States without degradation 5) feasibility of cathelicidn induction assay, testing subjects with T-SPOT.TB locally and confirmation of the prevalence of positive skin test at baseline.

Secondary endpoints for this study will be the absolute levels of serum 25(OH)D in the treated and control groups at baseline. Tertiary endpoints include paired differences between serum 25(OH)D at the baseline and end of the pilot study

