Treatment regimen: Subjects will be randomly assigned to receive a daily oral dose of one of two treatments from enrollment until the end of the study: (1) vitamin D (800 IU per day), or (2) placebo every school day for total nine months. All the experimental tablets will be identical in color but number-coded. The daily dose of vitamin D (800 IU) that we will use is well under the tolerable upper limit (TUL) of 2000 IU set by the institute of Medicine for children*, and is well below the level of human toxicity. The only known cases of toxicity have involved vitamin D intake greater than 40,000 IU/day. (21). **Standing Committee on the Scientific Evaluation of Dietary Reference Intakes FaNB, Institute of Medicine: Dietary Reference Intakes for Calcium, Phosphorus, Magnesium, Vitamin D, and Fluoride. National Academy Press, Washington, D.C., 1997. Available online at <http://books.nap.edu/openbook.php?record_id=5776&page=285>

Participant compliance monitoring: Substantial consideration has been given to the issue of adherence to the vitamin D intake protocol. First, 14 days after the participant is scheduled to begin taking supplementation they will be called to assess for any symptoms of toxicity. At that time, a series of brief questions will be asked to determine if the participant is having difficulty with adherence, and barriers will be addressed. Any participants who report having difficulty will be contacted again in 3 days to assess adherence and identify any additional strategies that might enhance adherence. Second, at the beginning of each month we will contact all participants and remind them that the next month of supplementation is about to begin, and address any concerns. Finally, children will take the supplementation in the class under teacher’s supervision. We will also collect any remainder pills and count those pills. Finally, we will assess compliance by self-report.

Blinding: Placebo will be provided in tablets, identical in size and appearance to vitamin D tablets. Blinded study medication will be packaged in bottles containing tablets to provide sufficient supply for each month, with overage. All site personnel will be blinded to the treatment arm assignment.

Receiving, storage, dispensing and return: Study subjects will be instructed to return all unused study supplementation in the bottle in which it was dispensed. The study research associate will be responsible for dispensing the study supplementation to participants

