Study visits including procedure/tests involved at each visit (e.g., blood test, x-rays, questionnaires)

Treatment randomization will be double blinded.

a) We will recruit 3 classrooms of 100 children, expecting a maximal drop-out/non-completion rate of 10%.

b) Children and parents will complete baseline enrollment forms that query age, gender, economic background, TB contact, medical history for exclusions, and history of BCG vaccination, vitamin and supplementation intake. As part of this proposal, we propose a feasibility study to pilot test the study questionnaires and instruments (i.e., consent forms, self-administered questionnaire on diet, and lifestyle factors) to be used in the subsequent study. Mongolia is one of the countries with the highest tuberculosis burdens in the Western Pacific region. The rapid increase of TB incidence is not only related to improved detection but is also connected with transition hardship and the increase of severe poverty in Mongolia. We believe that the lifestyle factors and nutritional status of the participants assessed by the anthropometric measurements will influence the TB infection rate. In addition to agreeing to take the supplements once a day for the period of nine months, the subjects must consent to undergo a tuberculin skin test (TST) according to national guidelines and provide two 8 ml blood samples.

c) A 8 ml of blood will be drawn and cooled immediately before transportation to the Central Scientific Research Laboratory (CSRL) for further processing for T-cell assay, and where they will aliquotted into 3 x 2 cryotubes, and frozen for vitamin D and cathelicidin assay. White cells will be extracted into a pellet and stored for future genetic analysis, with the collaboration of Mongolian colleagues and if approved by the MOH Ethical Review Board. A fasting blood sample is preferred but will not be an absolute requirement, as the study biomarkers are not appreciably influenced by fasting status.

d) Baseline and endpoint measures will include: height, skin-fold thickness, and weight. The study doctor will also assess clinical signs of rickets and vitamin D deficiency. The study procedures will occur in the local school doctor’s office in private

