**Summary of changes**

**AMENDMENT #1**

We increased the number of enrolled subjects from 100 to 120, and to include children with positive tuberculin skin tests (TST). In the original protocol, we have IRB approval to enroll 100 TST negative children. In our initial screening of 120 children, we found only 86 TST negative children. Given this high baseline rate of TST positivty (28%), which had been heretofore unknown in Mongolia, we would have had to screen at least 130 children to find 100 TST negative ones. However, our screening provided the first data of this kind ever for Mongolia. The high rate of TST positivity in clinically healthy children made it clearer to us than it had been before that a TST is useful clinically in Mongolia only if it is negative, because of the extensive use of BCG vaccination in that country.

Having found so many TST positive children, we felt we had an unanticipated ethical problem. Excluding the TST positive children from the study would have labelled them as possibly infected with active TB to their families, classmates, neighbors and teachers. The psycho-social consequences of that could be disaterous. By enrolling TST positive children in the study we would be providing greater protection for our subjects.

We therefore propose to update the inclusison/exclusion criteia as follows: eligible subjects will be children ages 12 to 15 years who attend public school # 65, located in the Songino-Khairhan district of Ulaanbaatar, and whose parents have given informed consent and who themselves assent to participate in the study. Exclusion criteria will be: pre-existing disorders of calcium metabolism, type I diabetes, sarcoidosis, chronic diuretic therapy including calcium channel blockers, or cognitive impairment.

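### Supplementation Study: the 90%-power detectable difference of 3.89 ng/ml does not fit the 80% figure beside it (3.05 on the same inputs), and the secondary 25(OH)D endpoint is timed at baseline

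*Supplement*

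**What the plan says.** All references are to the Protocol summary for the Supplementation Study and its amendments in the Supplement.

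- **Sample Size and Power Calculation.** The section gives "80% power to detect minimum detectible difference of 2.63 ng/ml and 90% power to detect minimum detectible difference of 3.89 ng/ml", "with an alpha error of 0.05". The SDs come from an earlier one-month intervention, with 25(OH)D of "17.3 + 4.8 at the outset of the intervention and 26.5 + 4.5 at the end", in ng/ml. It states no sample size, allocation ratio or sidedness. It refers to a table that is not shown in the text available to us.
- **Number of children.** Amendment #1 records the starting point: "In the original protocol, we have IRB approval to enroll 100 TST negative children". It then says "We increased the number of enrolled subjects from 100 to 120". The study-visits section plans on "expecting a maximal drop-out/non-completion rate of 10" percent, and the early-withdrawal paragraph removes withdrawn children's data from the analysis.
- **Arms.** "Subjects will be randomly assigned to receive a daily oral dose of one of two treatments from enrollment until the end of the study". The two treatments are vitamin D and placebo.
- **Study endpoints.** Feasibility is primary. "Secondary endpoints for this study will be the absolute levels of serum 25(OH)D in the treated and control groups at baseline". Paired differences between baseline and the end of the pilot are tertiary.
- **Statistical Analysis.** The main analysis takes each child's pre-to-post difference and compares the group means by t-test, with a Wilcoxon test as fallback.

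**The concern.** One sentence gives two detectable differences for the same outcome, alpha and pilot SDs, differing only in power. Moving from 80% to 90% power raises a detectable difference by a fixed proportion of about 16%. Here it rises by 48%, so at least one figure is wrong. The pilot is meant to supply preliminary data for a later application, and a reader planning that study would take the design's sensitivity from this sentence.

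The endpoint wording raises a related question about which quantity the calculation serves. The section powers a difference between arms after the intervention, while the secondary 25(OH)D endpoint is measured before any tablet is taken. Read literally, that endpoint carries no information on whether supplementation raises 25(OH)D, which is Aim B.

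**Working it through.** **Inputs**

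- SDs 4.8 and 4.5 ng/ml and alpha 0.05: Sample Size and Power Calculation.
- Two-sided test: assumed. It reproduces 2.63 at 50 per arm; a one-sided test gives 2.33.
- 50 per arm: inferred from 100 children in two arms at 1:1.
- 120 enrolled: Amendment #1. Loss of up to 10%: study-visits section.

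**Step 1: reproduce the 80% figure**

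Pooled SD = √((4.8² + 4.5²)/2) = √21.645 = 4.652.

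SE of the difference with n per arm = 4.652 × √(2/n). For n = 50 this is 0.930.

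Normal approximation: (1.960 + 0.842) × 0.930 = 2.61. Solving with the noncentral t on 98 degrees of freedom gives **2.633**, which matches the stated 2.63.

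**Step 2: the 90% figure on the same inputs**

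Normal approximation: (1.960 + 1.282) × 0.930 = 3.02. Noncentral t: **3.046**, against the stated 3.89. With 50 per arm, power at a true difference of 3.89 is 98.5%.

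**Step 3: a check that does not need the inferred sample size**

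n and SD enter only through the SE, which cancels in the ratio:

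(1.960 + 1.282)/(1.960 + 0.842) = 1.157 (one-sided: 1.177).

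The noncentral t gives 1.157 to 1.160 for any n from 5 to 195 per arm. The stated ratio is 3.89/2.63 = 1.479. For 3.89 to be the 90% figure with these SDs, about 31 per arm would be needed, and the 80% figure would then be 3.36.

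**Step 4: the sample after Amendment #1**

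120 less 10% is 108, or 54 per arm at 1:1.

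| Per arm | Basis | 80% power | 90% power |
|---|---|---|---|
| 50 | 100 enrolled, no loss | 2.63 | 3.05 |
| 54 | 120 enrolled, 10% loss | 2.53 | 2.93 |
| 60 | 120 enrolled, no loss | 2.40 | 2.78 |

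**Step 5: which SD applies**

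4.65 is the SD of a level at one time point, but the planned t-test is on change. With pre-post correlation r, the SD of change is √(4.8² + 4.5² − 2 × r × 4.8 × 4.5). The documents give no r, so the range is shown for 54 per arm.

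| r (assumed) | SD of change | 80% power | 90% power |
|---|---|---|---|
| 0 | 6.58 | 3.58 | 4.14 |
| 0.5 | 4.66 | 2.53 | 2.93 |
| 0.75 | 3.30 | 1.80 | 2.08 |

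The cross-sectional figures therefore carry over to the change-score test only when r is about 0.5.

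**Step 6: endpoint, power target and analysis side by side**

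- Secondary endpoint: level in each arm at baseline.
- Power calculation: difference in means between arms after the intervention.
- Main analysis: between-arm difference in within-child change.

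The first is not a treatment contrast. The second and third are, and differ mainly in the SD that applies (Step 5).

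**The case against.** **The power section states no sample size, and its table is not shown.** This is fair, and it makes 50 per arm an inference, though one supported by the match to 2.63. The missing table might show sample sizes or further rows. It cannot reconcile two figures given in one sentence for one design, because the ratio in Step 3 holds for any sample size and SD.

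**The consequence is small.** This largely stands. The primary endpoint is feasibility, the budget partly set the sample size, and 3.89 understates the design's sensitivity. Both figures lie well below the uncontrolled pilot rise of 26.5 − 17.3 = 9.2 ng/ml. A later application would also rely mainly on the means and SDs this pilot observes.

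**A reader might infer that drop-out and the larger sample were ignored and that power is short.** The documents do not support that. The 2.63 figure does correspond to 100 completers, and no text shown restates power for 120. But the amended plan expects at least 108 completers, which is more than 2.63 requires. A shortfall calculated on 45 per arm would describe the superseded 100-child design.

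**A reader might infer that the protocol cannot answer whether vitamin D raises 25(OH)D.** That goes too far. The Statistical Analysis section specifies a between-arm test of within-child change, and the tertiary endpoint supplies the data. Describing baseline levels is also a legitimate aim for a pilot, and the endpoint sentence does not say the arms will be tested against each other at baseline. What remains is that the higher-ranked 25(OH)D endpoint is not the one analysed for effect.

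**Conclusion.** The 90%-power figure is wrong as written. Taking 2.63 as the anchor, it should be 3.05 ng/ml; the stated 3.89 is 0.84 ng/ml too high and would have about 98.5% power. That the two figures are inconsistent is certain on any common sample size and SD. The value 3.05 rests on 1:1 allocation, 50 per arm and a two-sided test. The error is conservative, and with 54 completers per arm the design detects 2.53 and 2.93 at SD 4.65, so it gives no ground for calling the trial underpowered. How far those figures apply to the planned change-score test depends on a correlation the plan does not state.

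The baseline timing of the secondary endpoint is a lesser wording and ranking fault: Aim B has a specified randomised test, but the endpoint list does not give it that place.

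**What to change.** 1. In Sample Size and Power Calculation, either replace 3.89 with 3.05 and state 50 per arm, or, better, restate both figures for the amended sample: 2.53 ng/ml at 80% power and 2.93 ng/ml at 90%, for 54 completers per arm (120 enrolled, 10% loss, 1:1, two-sided 0.05).
2. Add that these figures use the cross-sectional SD of 4.65 ng/ml and apply to the planned t-test on change only if the pre-post correlation is about 0.5. If the sponsor holds paired pilot data, use the observed SD of change instead.
3. Reword the secondary endpoint as the between-arm difference in change in serum 25(OH)D from baseline to end of study. Keep baseline levels by arm as descriptive. This matches the existing analysis, which then needs no change.

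The cost is a few sentences of protocol text, with no change to sample size, data collection or analysis method.
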